### Study interventions

#### Standard of care

At study units assigned to the SOC arm of the study, participants were managed as per country guidelines. After testing HIV positive, individuals received post-test counseling and were referred to an HIV clinic using a national referral form that documents the patient’s identification and HIV status. Patients who linked to HIV care received clinical and laboratory assessments for the determination of ART eligibility, including CD4+ count testing and hematology and chemistry tests, and were instructed to return to the clinic in 1 to 2 weeks to receive their results. Upon return, those found eligible for ART initiation received three counseling sessions. The time interval from eligibility determination to ART initiation typically has been 1 to 2 months. All patients were given cotrimoxazole prophylaxis and those not eligible for ART were instructed to return every 3 months to the clinic, while those who initiated ART returned to the clinic every month for 6 months, and then every 3 months if they were stable on treatment. Peer counselors were encouraged to call patients within 7 days of a missed appointment; however, these procedures were often not consistently applied. Condoms and informational materials were available for all patients at HIV clinic visits.

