#### Combination intervention strategy

Participants at study units assigned to the CIS study arm received five evidence-based interventions in addition to SOC interventions. The five interventions include the following: (1) point-of-care CD4+ count testing on the same day as HIV diagnosis, (2) accelerated ART initiation for eligible patients with CD4+ count <350 cells/μL, the prevailing ART eligibility threshold during the conduct of the study, (3) mobile phone appointment reminders, (4) care and prevention bags, and (5) non-cash financial incentives for linkage and retention. Table 2 shows the interventions included in the study, the type of barrier addressed, and the target step in the HIV care continuum. Clinic staff at study units assigned to CIS were trained on each of these interventions and the importance of their provision to all study participants at their site.

**Table 2 Tab2:** Study interventions, type of intervention, and target step in the HIV care continuum

Intervention	Standard of care (SOC)	Combination intervention strategy (CIS)	Type of intervention	Step targeted in HIV care continuum
Point-of-care CD4+ count testing	• Point-of-care CD4 assays available in some primary care clinics and some secondary health centers/hospitals for patients enrolled in HIV care but only used once a patient has linked to care	• Point-of-care CD4 assays at the HIV testing site at the time of HIV testing	Structural and biomedical	Linkage and ART initiation
		• Turnaround time immediate		
	• All clinics have CD4 (Cyflow, FACS Caliber) availability after linkage to HIV care in the clinic or lab			
	• Turnaround time approximately 2 weeks			
Accelerated ART initiation	• ART initiation per national guidelines for patients with CD4 ≤350 cells/μL or WHO stage III/VI	• Accelerated ART initiation for patients with point-of-care CD4 ≤350 cells/μL within 1 week from testing	Structural and biomedical	ART initiation and retention
	• Requires 3 counseling sessions and receipt of baseline lab tests	• 2 counseling sessions (one at the time of HIV testing and another at the first HIV clinic visit), and collection of blood for other baseline lab tests, but ART initiation prior to return of results for patients who do not meet the criteria for waiting for receipt of lab results prior to ART initiation		
	• Initiation 2 weeks–1 month from testing			

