*Point-of-care CD4+ count testing*. Each participant at sites randomized to CIS received a point-of-care CD4+ count test immediately after testing HIV positive. The CD4+ count test was conducted by the study staff and took approximately 20 min to process. CD4+ count results and their implications were provided to the participant, and a copy was placed in the patient’s national referral form for HIV care. Regardless of the CD4+ count result, all participants were encouraged to link to HIV care within 1 week of receiving the results.*Accelerated ART initiation for eligible participants*. This intervention streamlined the preparatory procedures required for ART initiation by consolidating the ART counseling sessions into two sessions, as compared to three in standard of care, in order to enable ART initiation within 1 week of diagnosis. At sites assigned to CIS, the first ART preparatory counseling session was given at the time of receiving the point-of-care CD4+ count result at the HIV test site. The second session was given by the clinic staff at the HIV care site, at the first visit upon linkage to care by the participant. Clinic staff collected samples for the required baseline laboratory tests per national guidelines. Clinicians were encouraged to initiate ART at this first care visit, rather than awaiting the results of these laboratory tests in participants with no comorbid conditions. For participants that needed further counseling and/or clinical assessments, initiation of ART was done at the discretion of the clinician. Participants who initiated ART received a 2-week supply of medications per national guidelines. Baseline laboratory results were reviewed by the study staff with the clinic staff soon after availability, and if any abnormality was noted, participants were contacted to return to the clinic. After initiating ART, all follow-up visits followed national guidelines, similar to the standard of care procedures.*Mobile phone appointment reminders*. All participants at sites assigned to CIS received appointment reminders via mobile phone SMS, or voice message reminders for illiterate participants, to encourage linkage to care and completion of scheduled clinic visits. Reminders were sent to the participant’s phone or on a friend or relative’s phone per participant preference. The reminders did not refer to HIV or reveal any personal information. An example message is: “Good day – This is a reminder about your visit at [health facility] tomorrow. We look forward to seeing you then*.*” SMS were sent from a central server 1 day prior to scheduled clinic visit date for all participants. For participants who missed appointments, a text message was sent within 7 days to encourage the participant to return to the clinic.*Basic care and prevention package*. All participants at sites assigned to CIS received a package of commodities and informational materials upon linkage to care and once every 3 months thereafter during the study period. This package was designed to offer an opportunity to have further counseling on HIV care through provision of commodities that were deemed of value by the patients. Commodities in the package included condoms, a pillbox, soap, toothbrush and paste, cotrimoxazole tablets, and an appointment calendar. The health counseling that accompanied each package used existing national health information and educational materials (i.e., pamphlets, pictures) that focused on medication adherence, family planning, tuberculosis screening and cough hygiene, and nutrition.*Non-cash financial incentive (FI)*. All participants at sites assigned to CIS who linked to care within 1 month of HIV testing and those who completed HIV care clinic visits at 6 and 12 months after HIV testing received a non-cash FI in the form of prepaid mobile phone airtime vouchers. Each FI consisted of 80 Swaziland Emalangeni ($8–10), an amount selected based on the estimated cost of traveling to the clinic and with consultation with key stakeholders in the country.

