
### Data collection

All participants completed a baseline interview, at the time of study enrollment, which included information on sociodemographics, HIV history, barriers to care, travel time to clinic, depression, social and family support, and HIV-related knowledge. Follow-up interviews were conducted at home at 1 and 12 months after enrollment to collect information on changes in sociodemographic characteristics, utilization of HIV services including self-reported linkage to care and visit completion, and acceptability of the study interventions. A CD4+ cell count was obtained at 12 months. Additional clinical and laboratory data were extracted from paper-based patient medical charts. Facility assessment surveys were conducted at the beginning of the study and every 6 months to document any changes in clinical services that occurred during the study period that may influence study outcomes. Costs of delivering the SOC and CIS were estimated based on the cost of outpatient HIV care, the cost of hospitalization, and the cost of delivering each intervention component.

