### Sample size and power calculations

We estimated that 35 % of participants in the SOC study arm would achieve the combined primary outcome (assuming 50 % link to HIV care within 1 month and 70 % of those linking within 1 month are retained 12 months after study enrollment). We estimated that approximately 2750 adults would be eligible for study enrollment based on historic testing volume, the proportion testing HIV positive at the study units from 2010 to 2011. Assuming 80 % of eligible individuals consent to enroll in the study, we estimated an average enrollment of 220 participants per study unit or 2200 in total with 1100 per study arm.

With this sample size and five study units per study arm, we estimated the minimum difference in the primary outcome we could detect with 80 % power using a two-sided Farrington and Manning Likelihood Score Test [19], assuming an interclass correlation coefficient of 0.05. Estimates were made using the Power and Sample Size (Pass 8.0) software program. With these assumptions, the study has 80 % power to detect an absolute increase of 20 % or more in the CIS versus SOC arm on the primary outcome of linkage within 1 month and retention at 12 months.

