### Statistical methods

An intent-to-treat analysis was planned to compare the relative risk of achieving the primary outcome of linkage to care within 1 month and retention in care at 12 months after HIV testing. The effectiveness of CIS compared to SOC will also be assessed on secondary outcomes including the following: linkage to care within 1 month; retention 12 months after HIV diagnosis; and time from ART eligibility to ART initiation, viral load suppression 12 months after HIV diagnosis, disease progression, and cost-effectiveness. Sub-distribution hazard models, treating death as a competing risk for ART initiation, are to be used to compare the time from eligibility to initiation of ART between participants receiving CIS and SOC, with participants transferring or becoming lost to follow-up after ART eligibility but before initiation censored at their date of transfer or their last recorded visit. Robust sandwich estimates of variance will be used to account for correlation within study units. Sociodemographic and clinical determinants of the primary and secondary outcomes are to be analyzed to examine whether the CIS differentially impacts outcomes within strata by sociodemographic and clinical characteristics (e.g., age, sex, HIV disease stage, CD4+ count, tuberculosis, and pregnancy status). We will conduct covariate-adjusted generalized linear mixed models if important differences are observed between study arms in order to assess the degree to which these differences influence outcomes. For cost-effectiveness analysis, a model will be created to estimate the effect of CIS on health benefits and costs. Differences in life expectancy, quality-adjusted life years, and infections averted between CIS and SOC arms will be estimated using inputs from the study.

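### CD4 count is a planned stratifier of the intervention effect, but in the standard-of-care arm it exists only for participants who have linked to care

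*Protocol article*

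**What the plan says.** Under Statistical methods, the protocol article plans to analyse determinants of the primary and secondary outcomes, to see "whether the CIS differentially impacts outcomes within strata by sociodemographic and clinical characteristics (e.g., age, sex, HIV disease stage, CD4+ count, tuberculosis" and one further item). The same section adds: "We will conduct covariate-adjusted generalized linear mixed models if important differences are observed between study arms". It names no covariates for those models and gives no rule for participants without a value.

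The arms differ in when CD4 is measured:

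- CIS (Combination intervention strategy): "Each participant at sites randomized to CIS received a point-of-care CD4+ count test immediately after testing HIV positive".
- SOC, point-of-care assays (Table 2): available in some facilities "for patients enrolled in HIV care but only used once a patient has linked to care". The same table places laboratory CD4 after linkage as well.
- SOC narrative (Standard of care): "Patients who linked to HIV care received clinical and laboratory assessments for the determination of ART eligibility, including CD4+ count testing".
- Both arms (Data collection): "A CD4+ cell count was obtained at 12 months. Additional clinical and laboratory data were extracted from paper-based patient medical charts". The listed contents of the baseline interview include none of CD4, disease stage or tuberculosis.

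Study objectives and outcomes defines linkage as a clinic visit with a completed intake history and examination. Linkage within 1 month is one half of the combined primary outcome and also a secondary outcome.

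**The concern.** A stratifier of a randomised effect should be known for everyone, in the same way in both arms, before the outcome begins to unfold. CD4 does not meet that condition here. In CIS a value exists whether or not the person ever reaches a clinic. In SOC a value exists only if the person has linked, so having one depends on part of the outcome being compared. Participants in SOC who never link are outcome failures with no CD4 stratum to sit in, while their CIS counterparts stay in and count as failures.

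A CD4-stratified comparison of linkage, retention or the combined outcome is therefore tilted against CIS. If SOC linkage also varies with CD4, the tilt differs between strata and looks like effect modification. Such results could influence whom the strategy is offered to.

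**Working it through.** **The plan's own figures** (Sample size and power calculations). "We estimated that 35 % of participants in the SOC study arm would achieve the combined primary outcome". That rate is the product of two planning values, early linkage of 50% and 12-month retention of 70% among early linkers: 0.50 × 0.70 = 0.35. The detectable increase is 20 points, so CIS is 0.55 and the risk ratio (RR) is 0.55/0.35 = 1.57. With 220 per unit, five units per arm and an intraclass correlation of 0.05, the design effect is 1 + 219 × 0.05 = 11.95, and the effective size per arm is 1100/11.95 = 92.05. At an assumed two-sided 5% level, power for 35% versus 55% is 78.3% (pooled variance) or 79.5% (unpooled), which reproduces the stated 80%.

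**CD4 strata, combined outcome.** Let f be the share of SOC participants who ever have a CD4 result. The article does not give f. The planning 50% is linkage within 1 month only; later linkers also get a CD4 count, so f is shown over a range. Two working assumptions: every SOC success has a CD4 result, since each has linked, and participants without a value are left out.

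- SOC success among those with CD4 = 0.35/f
- CIS success among those with CD4 = 0.55/1
- Observed RR = 0.55/(0.35/f) = 1.57 × f

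| f (assumed) | SOC with CD4, of 1100 | SOC success | CIS success | Observed RR |
|---|---|---|---|---|
| 50% | 550 | 70.0% | 55% | 0.79 |
| 60% | 660 | 58.3% | 55% | 0.94 |
| 70% | 770 | 50.0% | 55% | 1.10 |
| 80% | 880 | 43.8% | 55% | 1.26 |
| 100% | 1100 | 35.0% | 55% | 1.57 |

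Break-even is f = 0.35/0.55 = 63.6%. Linkage within 1 month is distorted in the same way: the planned SOC rate of 50% becomes 0.50/f, which is 100%, 83%, 71% and 63% at f = 50%, 60%, 70% and 80%.

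**False effect modification.** Suppose the true RR is 1.57 in both of two CD4 strata, and SOC CD4 is known for 60% of the low and 40% of the high stratum (assumed). The observed RRs are 1.57 × 0.60 = 0.94 and 1.57 × 0.40 = 0.63, a difference produced by availability alone.

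**Disease stage and tuberculosis.** If these are known only for linkers in both arms, observed RR = 1.57 × (SOC share known)/(CIS share known). With SOC at 50% and 70% retention among linkers in both arms, CIS linkage must be 0.55/0.70 = 78.6%, and RR = (0.55/0.786)/(0.35/0.50) = 1.00: the linkage effect is removed. The sign reverses only if CIS linkage exceeds 78.6% with SOC at 50%. With SOC at 70%, even 95% in CIS gives RR 1.16.

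**The case against.** The main analysis is not at issue. The primary outcome is compared by intention to treat, and the criticised sentence is a secondary analysis of determinants with an illustrative list. Dropping participants without a value is the software default, not a stated rule, and an analysis plan that is not shown may handle missing covariates differently. The adjusted models are contingent and name no covariates. Not all secondary outcomes share the problem in this form: time from ART eligibility to initiation is already defined only among people assessed as eligible.

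All of this stands and limits the point. It does not remove it, because CD4 is named as a stratifier and the text fixes when it is measured in each arm. Missing-data methods offer only a qualified rescue: no SOC participant who never linked has a baseline CD4, so imputation would have to borrow the relation between CD4 and outcome from SOC linkers or from CIS, which is close to assuming the answer to the interaction question. The 12-month CD4 is measured after the intervention and cannot stand in for a baseline value.

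Stronger readings are tempting but not supported:

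- *The analysis will show CIS as harmful.* Reversal needs fewer than 63.6% of SOC ever to have a CD4 result, and the article does not give that share.
- *Stage and tuberculosis are recorded only after linkage.* This is inferred from the content of the intake visit, the chart abstraction and the listed interview items. The interview's HIV history item is not detailed.
- *The adjusted models are biased.* They are affected only if these variables trigger or enter them. A CD4 difference between all of CIS and SOC linkers could arise from selection alone, but the article does not say that CD4 would be tested or entered.

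**Conclusion.** The point holds for CD4 strata of outcomes that include linkage or retention. As planned, and with participants lacking a value left out, such strata understate the CIS effect by the factor f: RR 1.57 becomes 0.79 to 1.26 for an assumed f of 50% to 80%. Attenuation occurs at every share below 100%; reversal only below 63.6%. The size rests on the planning rates and on every SOC success having a CD4 result.

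For disease stage and tuberculosis the problem is probable but not established, and loss of the linkage effect is the plain result under equal retention. The unadjusted intent-to-treat comparison and the age and sex strata are sound on this point. This is a defect in a secondary analysis that should be corrected; it does not threaten the trial's main conclusion.

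**What to change.** For the linkage, retention and combined outcomes:

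- Limit effect-modification and covariate-adjusted analyses to characteristics recorded at enrolment for everyone in both arms: age, sex and baseline-interview items.
- Take CD4 count out of the stratification list, the adjustment set and the arm-difference trigger. Do the same for disease stage and tuberculosis unless they were recorded at enrolment in both arms.
- Report these variables descriptively by arm, with the number missing in each.
- If a CD4-specific effect is still wanted, label it exploratory, keep unlinked SOC participants in the denominator under stated assumptions, and give a sensitivity range.

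The cost is analysis-plan wording. Enrolment is complete, so the missing SOC values cannot be collected now, but the article describes follow-up as still running, so the analysis could still be changed at that stage. The downside is losing an unqualified CD4-stratified effect estimate.

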**Fig. 1 Fig1:**
[figure not shown]
Link4Health study units

**Table 1 Tab1:** Study unit matched pairs

Matched pair	Study unit	Study arm	Implementing partner	Location
1	1	SOC	Partner A	Urban
	2	CIS	Partner A	Urban
2	3	SOC	Partner A	Urban
	4	CIS	Partner A	Urban
3	5	SOC	Partner A	Rural
	6	CIS	Partner A	Rural
4	7	SOC	Partner A	Rural
	8	CIS	Partner A	Rural
5	9	CIS	Partner B	Urban
	10	SOC	Partner B	Urban

*SOC* standard of care, *CIS* combination intervention strategy

Individuals who tested HIV positive at HIV testing sites located at the study unit received post-test counseling and were referred to the study by clinic staff. Thereafter, the study research staff provided an overview of the study, conducted eligibility screening, and conducted informed consent procedures. Study eligibility criteria included the following: HIV-positive test, ≥18 years of age, willing to receive HIV care at a clinic in the study unit, and consent to study procedures. Study exclusion criteria included the following: planning on leaving the community during the study period for more than 6 months, enrolled in HIV care and/or initiated ART in the past 6 months, currently on ART, does not speak English or SiSwati, or current pregnancy.

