### Study objectives and outcomes

The primary study objective was to evaluate the effectiveness of the CIS compared to SOC on the combined outcome of linkage to HIV care within 1 month of an HIV-positive test and retention in care at 12 months among adults diagnosed with HIV. Linkage to care was defined by at least one visit to HIV clinic with completion of an intake assessment including medical history and physical exam. Retention in care at 12 months after HIV testing was defined as a clinic visit within 90 days prior to the end of the study follow-up period.

The secondary objectives included the evaluation of the effectiveness of CIS compared to SOC with regard to the following: linkage to care within 1 month after testing HIV positive, retention in care at 12 months after testing HIV positive, time to ART eligibility and ART initiation, viral load suppression at 12 months after HIV testing, disease progression, patient acceptability, and cost-effectiveness. Additionally, the effect of sociodemographic and clinical determinants on key study outcomes was to be assessed.

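### CD4-stratified effects on linkage, retention and the composite set all CIS participants against SOC linkers only, which biases them against CIS

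*Protocol article*

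**What the plan says.** Statistical methods commits to asking whether CIS acts differently on the primary and secondary outcomes "within strata by sociodemographic and clinical characteristics (e.g., age, sex, HIV disease stage, CD4+ count, tuberculosis, and pregnancy status". Under Study objectives and outcomes, the primary outcome combines linkage within 1 month with retention at 12 months. Each of the two is also a secondary outcome.

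When CD4 becomes known differs by arm:

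- CIS (Combination intervention strategy): "Each participant at sites randomized to CIS received a point-of-care CD4+ count test immediately after testing HIV positive".
- SOC (Standard of care): "Patients who linked to HIV care received clinical and laboratory assessments for the determination of ART eligibility, including CD4+ count testing". Table 2 adds that point-of-care assays exist at some SOC facilities "but only used once a patient has linked to care", and for laboratory CD4: "All clinics have CD4 (Cyflow, FACS Caliber) availability after linkage to HIV care in the clinic or lab".

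The baseline interview, as listed under Data collection, names no CD4, stage or tuberculosis item. The only study CD4 named there is at 12 months. For the rest: "Additional clinical and laboratory data were extracted from paper-based patient medical charts". Linkage itself requires "completion of an intake assessment including medical history and physical exam". The exclusion criteria under Study design end with "does not speak English or SiSwati, or current pregnancy".

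**The concern.** A stratified treatment effect is a randomised comparison only if membership of the stratum is settled, and observable, in the same way in both arms. Here a CIS participant has a CD4 value whether or not he or she links, while a SOC participant has one only by linking. Linkage within 1 month is one half of the primary outcome and a secondary outcome in its own right, and retention is not possible without linking at some point. Following the plan therefore removes from the SOC side of each CD4 stratum people who are certain failures, and removes no comparable people from the CIS side.

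At stake is the statement about whom the strategy helps. The Background suggests that a CD4 result may motivate linkage, particularly in patients found eligible for treatment, so readers will look for a CD4 subgroup result.

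**Working it through.** **Inputs.** From Sample size and power calculations: SOC linkage within 1 month 0.50; retention among those linkers 0.70; SOC composite 0.35; detectable increase 0.20, so CIS 0.55; 220 per unit, 5 units and 1100 participants per arm; intraclass correlation 0.05. Alpha is not stated; 0.05 two-sided is assumed.

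**The plan's own figures.** 0.50 × 0.70 = 0.35, as stated. Design effect = 1 + (220 − 1) × 0.05 = 11.95; effective n = 1100 / 11.95 = 92.05 per arm. Normal-approximation power for 35% v 55% is 78.3% (pooled variance) or 79.5% (unpooled), which agrees with the stated 80%. Using 55% for CIS is therefore consistent with the plan.

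**Selection in CD4 strata.** Let L be the share of SOC participants who ever get a CD4. Assume that participants with unknown CD4 are left out, and that every SOC participant who meets the composite has a CD4. Nobody meets the composite without linking, so all SOC successes stay in and only failures drop out:

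- SOC rate among those with a CD4 = 0.35 / L
- CIS rate = 0.55, over everyone
- Observed overall RR = 0.55 × L / 0.35; true RR = 0.55 / 0.35 = 1.57

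| L | SOC rate with CD4 known | Observed RR | Observed difference |
|---|---|---|---|
| 0.50 | 70.0% | 0.79 | −15.0 points |
| 0.60 | 58.3% | 0.94 | −3.3 |
| 0.70 | 50.0% | 1.10 | +5.0 |
| 0.80 | 43.8% | 1.26 | +11.3 |
| 0.90 | 38.9% | 1.41 | +16.1 |
| 1.00 | 35.0% | 1.57 | +20.0 |

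The observed RR equals 1 at L = 0.35 / 0.55 = 0.636. The row L = 0.50 requires that no SOC participant links after the first month.

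**Linkage within 1 month.** If CIS retention among linkers is also 70% (assumption), CIS linkage is 0.55 / 0.70 = 0.786 and the true RR is 0.786 / 0.50 = 1.57. With SOC linkage among those with a CD4 equal to 0.50 / L, the RR is 0.79 at L = 0.50 and 1.10 at L = 0.70. At L = 0.50 the SOC rate is 100% by construction, so no CIS effect could give an RR above 1.

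**Effect on the comparison between strata.** An illustration with assumed inputs: half the participants have low CD4; 1-month linkage in low/high CD4 is 0.60/0.40 in SOC and 0.886/0.686 in CIS; retention is 0.70; and 20% of SOC non-linkers link late and get a CD4.

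- Low CD4: CIS 0.886 × 0.70 = 0.620; SOC 0.60 × 0.70 = 0.420; SOC share with CD4 = 0.60 + 0.40 × 0.20 = 0.68, giving an observed SOC rate of 0.420 / 0.68 = 0.618. RR falls from 1.48 to 1.00.
- High CD4: CIS 0.686 × 0.70 = 0.480; SOC 0.40 × 0.70 = 0.280; SOC share with CD4 = 0.40 + 0.60 × 0.20 = 0.52, giving 0.280 / 0.52 = 0.538. RR falls from 1.72 to 0.89.

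The distortion differs by stratum, so the apparent effect modification is biased as well as its level. In this example the stratum with the larger RR changes from high to low CD4.

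**Stage and tuberculosis.** If these are charted only after linkage in both arms, the comparison is linkers with linkers: RR = (0.55 / Lc) / (0.35 / L), where Lc is CIS ever-linkage. With L = 0.50, RR is 1.31 at Lc = 0.60, 1.05 at 0.75 and 0.98 at 0.80. With L = 0.70 and Lc = 0.60 it is 1.83. The effect can be attenuated or inflated, depending on linkage in each arm.

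**The case against.** The strongest reply concerns size and scope.

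- The 50% in the sample-size section is linkage within 1 month, whereas a charted CD4 depends on ever linking during follow-up. The documents do not give that share. A reader might infer from the 50% and 70% figures that the CD4 strata will show harm; they do not support that, because reversal needs L below 63.6%. This stands.
- The arithmetic assumes that unknown CD4 is dropped. Statistical methods does not say so, and handling of a missing stratifier is commonly left to an analysis plan, which is not shown. This also stands, but the alternatives do not rescue the comparison. An unknown-CD4 category would hold SOC non-linkers, with no successes, and essentially no CIS participants. Imputation would rest on untestable assumptions about SOC non-linkers. The 12-month CD4 is post-intervention.
- A reader might extend the comparison of all CIS participants with SOC linkers to stage and tuberculosis. The documents do not support that. The intake examination and chart extraction suggest recording after linkage in both arms. Even this timing is inferred, since the items under HIV history in the baseline interview are not listed.
- Adjusted mixed models are planned only if important differences between arms appear, and no covariates are named. That CD4 would enter them is a possibility, not a stated plan.
- Pregnancy status has no time point, so it may mean pregnancy during follow-up. It is a minor point of wording.
- The strata are given as examples for a secondary analysis, and overall effectiveness does not depend on them. This stands and limits the seriousness.

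**Conclusion.** The concern holds for CD4-stratified effects on linkage, retention and the composite. As described, these are not comparisons of randomised groups, and they are biased against CIS whenever some SOC participants never get a CD4 and are left out. With the plan's rates, a true RR of 1.57 would appear as 0.79 to 1.41 for L from 0.50 to 0.90; it is attenuated throughout and reversed only below L = 63.6%. This rests on L, which is an assumption, on exclusion of unknown CD4, and on every SOC success having a CD4. No figure is given for retention alone, because the documents give no overall SOC retention rate; the direction is the same, since SOC participants who never link are not retained and drop out.

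Stage and tuberculosis strata probably carry a different post-randomisation selection, of uncertain size and direction. The unstratified intent-to-treat comparison and the age and sex strata are unaffected, so a reader should not infer that the main result is in doubt. The point should be fixed before analysis, but it does not threaten the trial's primary conclusion.

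**What to change.** Add to Statistical methods, or to the analysis plan, that for linkage, retention and the composite:

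- effect-modification strata, and any adjustment covariates, are limited to variables recorded for everyone at enrolment (for example age, sex and the baseline interview items);
- CD4 results, and stage and tuberculosis if these are recorded only after linkage, are reported descriptively or as a labelled non-randomised comparison, with the number unknown by arm;
- pregnancy status is dropped as a baseline stratum, since current pregnancy is an exclusion, or is labelled as a follow-up event.

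The article reports follow-up as still under way, so this can be settled before analysis. It takes a few lines of text. What is given up is the CD4 subgroup claim on these outcomes, which the data as described cannot validly support.
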